## 14.2 Analysis Population

In phase 2 the primary analysis will be conducted on outcome data obtained from randomised participants who receive at least some of their randomly allocated treatment. It is possible that some subjects may not receive the full treatment dose. Therefore a secondary analysis will be undertaken on the population who receive the complete treatment dose. An additional analysis in the COVID-19 cohort will also be conducted on patients who have a confirmed PCR diagnosis of COVID-19. For the COVID-19 cohort even if an additional risk factor for ARDS co-exists, these patients will be included in the COVID-19 cohort. A patient will be analysed according to the cohort to which they were randomised. A priori defined subgroup analyses will be undertaken based on severity of inflammation as measured by plasma CRP and ferritin.

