### **10.3 Blinding**

The cell therapy facility and clinical trials pharmacist will be unblinded. The unblinded individuals will keep the treatment information confidential and will not discuss or release information on treatment allocation to the patient, the investigator, or other members of the research team.

As in prior studies of MSCs (48, 66), the infusion bag containing either the cell product or placebo will be masked at the time of preparation in the clinical site's cell therapy facility so that the contents of the infusion bag are not visible to the investigators or to the clinicians who

are administering the study drug. The contents of the infusion bag will be administered through a masked infusion set.

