| 6 | How               | 
The REALIST ORBCEL-C substance will be thawed and re-suspended in Plasma-Lyte 148 in the clinical site's cell therapy facility by the cell therapy facility staff according to the Product Specification.
 
The cell therapy facility or site pharmacy staff will be responsible for preparing the Plasma-Lyte 148 placebo.
 
The study drug infusion should be commenced as soon as possible after delivery to site ICU and infusion completed within 6 hours of the start of the thaw procedure.
 
A single dose of the study drug will be administered intravenously over approximately 30 to 90 minutes.
 
Only 1 patient will be treated at a time. For the phase 1 trial, the CTU will manage the recruitment process and will communicate to sites when a patient can be recruited to ensure only 1 patient across all sites is treated at a time and that each patient will receive treatment no less than 24 hours following the completion of treatment of another patient. This does not apply to the phase 2 trial.
 
A single dedicated infusion line should be used for cell administration. The study drug can be infused via peripheral or central venous access, though if administered through a peripheral intravenous access, it should be at least 20-gauge, and ideally 18-gauge. The cells are administered through a standard blood filter tubing set with a 170 to 260 micron filter.
 |

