### 12.2 Study Visits and Procedures

#### Day 0 (Baseline)

Baseline data (day 0) is the 24 hours preceding the time of recruitment which is defined as the time of study drug administration. If more than one value is available for this 24-hour period the value closest but prior to the time of study drug administration will be recorded. Day 0 (baseline) data collected will include but is not limited to:

- Patient demographics
- Date of birth, gender, height, weight, PBW
- ICNARC Case Mix Programme (CMP) number or equivalent
- Date and time of ICU admission
- Date/time of onset of mechanical ventilation
- Date/time of consent and enrolment (phase 1) or randomisation (phase 2)
- Aetiology of ARDS
- The Acute Physiology And Chronic Health Evaluation score II (APACHE II)
- First qualifying P/F ratio (including date/time)
- Worst P/F ratio (including date/time)
- Murray Lung Injury Score
- Determinants of the SOFA score
- Temperature
- Ventilation parameters including but not limited to: Mode of ventilation, minute volume, RR, mean airway pressure, plateau pressure, PEEP
- Arterial blood gas including but not limited to FiO2, PaO2, PaCO2, pH, lactate
- Oxygenation Index
- Use of adjunctive therapies
- Renal replacement therapy
- Clinical laboratory assessments: renal, liver function, ferritin and CRP, haematological and coagulation parameters where possible
- Blood for anti-HLA antibodies will be collected where possible
- Echocardiography parameters (during phase 2 study only) including but not limited to ventricular size and function and tricuspid annular plane systolic excursion (TAPSE) will be collected where possible.
- Clinical or PCR diagnosis of COVID-19

Baseline blood, urine and BAL for translational studies will be taken (where possible) prior to study drug administration. Sampling procedures are outlined below.

## Day 1

Day 1 is from the time of recruitment (study drug administration) to the end of that calendar day. If more than one value is available for this period, the value closest but after the time of administration will be recorded. The following data will be recorded:

- Date/time of expiry of the study drug.
- Date/time of commencing the infusion of the study drug.
- Date/time of completion of infusion of the study drug.
- Study drug administration.

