## **14 STATISTICAL CONSIDERATIONS**

### **14.1 Sample Size**

The phase 1 trial will recruit up to 18 participants.

Although the primary focus of the phase 2 trial is safety, there is, however, power to detect a difference in physiological outcomes.

The sample size for the phase 2 REALIST trial is 60 patients with ARDS due to COVID-19 and 60 patients with ARDS not due to COVID-19 (30 in each of the ORBCEL-C and placebo groups). The recruitment, randomisation, treatment, outcome measurement and reporting, and follow-up processes will be as streamlined as possible.

Due to the clinical differences in patients with ARDS due to COVID-19 and other causes of ARDS, patients with ARDS due to COVID-19 and other causes of ARDS will be recruited as separate cohorts. This will also facilitate timely reporting of the results from each cohort.

The primary efficacy outcome measure will be the difference in oxygenation index (OI) between the ORBCEL-C and placebo treated groups at day 7. Based on our data from a recently completed clinical trial in ARDS, the mean (standard deviation; SD) OI at day 7 in patients with ARDS is 62(51)cmH2O/kPa [4]. To allow 1:1 recruitment (ORBCEL-C vs placebo) a sample size of 56 subjects will have 80% power at a two-tailed significance level of 0.05 using a two-sample t-test to detect a clinically significant difference of 39 cmH2O/kPa in OI between groups. In a previous phase 2 study of similar size, we have found that an intervention can demonstrate a change in OI of a similar magnitude confirming a treatment effect of this size can be achieved [4]. Although we anticipate few withdrawals or loss to follow-up we have allowed for this in the sample size calculation. In previous UK multicentre studies in the critically ill <3% withdrew consent or were lost to follow-up [4, 65] and on this basis a conservative drop-out rate of 5% has been estimated. Therefore a total of 60 evaluable patients who have received study drug (30 patients in the ORBCEL-C and 30 in the placebo group) will be recruited into each cohort.

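### The primary analysis leaves out randomised patients who were never infused, and preparation failure or delay can differ by arm, so the efficacy comparison is open to bias of unknown size

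*Protocol*

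**What the plan says.** Section 14.2 fixes the phase 2 primary set: "the primary analysis will be conducted on outcome data obtained from randomised participants who receive at least some of their randomly allocated treatment". It adds that "a secondary analysis will be undertaken on the population who receive the complete treatment dose", which is a narrower set. No analysis of all randomised patients is named. The sentence in 14.2 on analysing patients by the cohort to which they were randomised concerns the COVID-19 and non-COVID-19 cohorts, and does not bring uninfused patients back. Section 14.1 likewise counts only patients who have received study drug towards the 60 per cohort.

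Section 11.1, Table 1, allows a gap between enrolment and infusion, ideally no longer than 12 hours (item 8). Item 6 describes thawing and resuspension for the cell product only and requires "infusion completed within 6 hours of the start of the thaw procedure". It describes no thaw for the Plasma-Lyte placebo. Section 11.5 lists product expiry, death or discontinuation of active treatment, and a clinician's safety decision among the grounds for discontinuing study drug.

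Section 12.2 anchors day 0 to "the time of recruitment which is defined as the time of study drug administration". Ventilator-free days (VFDs), time to extubation, duration of ventilation and lengths of stay are all counted from the same moment.

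**The concern.** Leaving out randomised patients who were never treated is harmless when the chance of being treated cannot depend on the arm, or when those left out have the same prognosis as those kept. Neither is assured here. A failed thaw can happen only in the cell arm, and a longer or repeated cell preparation gives an unstable patient more time to die or become unsuitable before infusion. Losing such patients from the cell arm alone would make that arm look healthier on OI, VFDs and mortality.

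The outcome clock adds to the problem. A patient who is randomised but never infused has no day 0, and so no defined day-7 OI and no defined VFD count.

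**Working it through.** **Plan's own figure.** Section 14.1 gives a day-7 OI SD of 51, a difference of 39 cmH2O/kPa and 5% drop-out, and states that "a sample size of 56 subjects will have 80% power at a two-tailed significance level of 0.05 using a two-sample t-test". The exact two-sample t-test gives 27.84, so 28 per arm or 56 in total, with power 80.2%. Allowing for drop-out, 28/0.95 = 29.5, so 30 per arm or 60. Power at 30 per arm is 83.0%. The stated figures reproduce.

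**Bias from exclusion.** Let 30 patients be infused in each arm and k further cell-arm patients be randomised but not infused.

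- Share of the randomised cell arm excluded: f = k/(30 + k).
- D = mean OI of the excluded minus mean OI of the retained patients.
- Exclusion lowers the cell-arm mean by s = f × D.
- Standard error of the difference: SE = 51 × √(2/30) = 13.17.
- With no true effect, type I error = Φ(−1.96 − s/SE) + 1 − Φ(1.96 − s/SE).

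For k = 3 and D = 51 (1 SD): f = 3/33 = 9.1%, s = 0.0909 × 51 = 4.6, s/SE = 0.35, type I error 6.4%.

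| k | f | s at 1 SD (share of 39) | Type I error, D = 0.5 SD | D = 1 SD | D = 2 SD |
|---|---|---|---|---|---|
| 1 | 3.2% | 1.6 (4%) | 5.0% | 5.2% | 5.7% |
| 2 | 6.3% | 3.2 (8%) | 5.2% | 5.7% | 7.7% |
| 3 | 9.1% | 4.6 (12%) | 5.4% | 6.4% | 10.8% |
| 5 | 14.3% | 7.3 (19%) | 5.9% | 8.6% | 19.8% |

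If D = 0, then s = 0 whatever k is, even when every failure is in the cell arm.

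**Price of including everyone.** If uninfused cell-arm patients gain nothing, the effect becomes 39 × (1 − f).

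| k | Effect | Power, 30 + k cells vs 30 placebo | Total N for 80% power before drop-out |
|---|---|---|---|
| 0 | 39 | 83.0% | 56 |
| 1 | 37.7 | 81.1% | 60 |
| 2 | 36.6 | 79.3% | 64 |
| 3 | 35.5 | 77.4% | 68 |
| 5 | 33.4 | 73.7% | 76 |

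The protocol supplies the SD, the difference and the 30 per arm. The values of k and D, the placement of all failures in the cell arm and the absence of benefit in the uninfused are assumptions.

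**The case against.** The strongest reply is that bias needs two conditions, and the protocol shows at most one of them. A purely technical thaw failure removes a patient unrelated to prognosis and shifts nothing. The route most tied to prognosis, a bedside decision not to start in an unstable patient, is taken blind. Section 10.3 says that "The cell therapy facility and clinical trials pharmacist will be unblinded", but the bag and infusion set are masked from investigators and from the clinicians who give the infusion. This stands, and it narrows the concern to failure or delay arising before the product reaches the bedside.

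It is also fair that phase 2 is primarily about safety, for which a treated set is natural, that 14.1 is written consistently with such a set, and that CONSORT reporting and a detailed statistical analysis plan are promised. That plan, not at hand here, may add a sensitivity analysis. Section 14.2 nevertheless sets the primary population itself, for efficacy as well as safety.

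A reader might infer more than the text supports:

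- **Expiry affects only the cell arm.** Sections 11.4, 11.5 and 12.2 write expiry for study drug generally. Only the thaw, and the limit counted from it, are specific to cells. Whether placebo bags carry a matched expiry is not stated.
- **No all-randomised analysis is possible.** Time of randomisation, date of death, and 28- and 90-day mortality are collected (12.2, 12.4), so mortality can be analysed from randomisation. The gap is in day-7 OI and VFDs.
- **Pre-infusion deaths would hide a mortality difference.** Any such example rests on chosen counts, because the protocol gives no number of uninfused patients in either arm.

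**Conclusion.** The point holds as a weakness in a stated rule. The primary efficacy set is defined by an event after randomisation, that event can depend on the arm through cell preparation, and delay offers a plausible link to prognosis. The comparison is therefore open to bias. The documents do not show that bias will occur or that randomisation is broken.

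The size cannot be fixed, because no non-infusion rate or preparation time is given. Under the assumptions above, one or two exclusions at 1 SD worse prognosis take the type I error only to 5.2% or 5.7%, and five take it to 8.6%. Anything near 20% needs both five exclusions and a 2 SD difference. The change is worth making because it is cheap and removes a question that the results could not settle afterwards.

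**What to change.** - **Section 14.2:** analyse efficacy in all randomised patients by allocated arm, as the primary set or at minimum as a prespecified sensitivity analysis. Keep the set that received any study drug for safety.
- **Section 12.2:** for patients never infused, set day 0 at randomisation, which is already recorded. Collect their day-7 status and OI where available, VFDs, and 28- and 90-day mortality. A patient who dies before day 7 has no OI under either population, so including such patients adds their status but no OI measurement.
- **Reporting:** give the number not infused, with reasons, by arm.

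The cost is wording in two sections, follow-up of a few extra patients and the slight dilution shown above: with 1 to 3 uninfused cell-arm patients the effect falls from 39 to between 37.7 and 35.5.

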## 14.3 Statistical Methods

For the Phase 1 trial no formal statistical analysis will be performed on safety data. The primary analysis will be descriptive and will focus on adverse events. The number of pre specified cell infusion associated events will also be reported. Descriptive analysis of pulmonary and non-pulmonary organ function will also be undertaken. We plan to publish the data from the phase 1 study.

The maximal tolerated dose up to 400x10^6cells will be proposed by the TMG and approved by the DMEC prior to use in the Phase 2 randomised controlled clinical trial.

For the Phase 2 trial, adverse events and prespecified cell infusion associated events will be reported as for the Phase 1 study in a descriptive analysis. For continuously distributed outcomes, differences between groups will be tested using independent samples t-tests and analysis of covariance with transformations of variables to normality if appropriate, or non-

parametric equivalents. Chi-square tests (or Fisher's Exact tests) will be used for categorical variables. A p value of 0.05 will be considered as significant.

Correlations between changes in the biological markers measured and physiological and clinical outcomes will be assessed by appropriate graphical and statistical methods including Pearson's (or Spearman's) correlation coefficient.

A final analysis and report of the Phase 1 study is planned following the last patient's 90 day follow up. A final analysis and report of the phase 2 study is planned following the last patient's 90 day follow up. The 2 year follow up data will be published thereafter and will be an important long term outcome. Detailed statistical analysis plans for phase 1 and phase 2 will be written and approved by the independent DMEC prior to any analysis.

All the power calculations and methodology for data analysis have been confirmed by the trial statistician from the Northern Ireland Clinical Trials Unit (NICTU).

#### 14.4 Missing Data

Every effort will be made to minimise missing baseline and outcome data in this trial. The level and pattern of the missing data in the baseline variables and outcomes will be established by forming appropriate tables and the likely causes of any missing data will be investigated. This information will be used to determine whether the level and type of missing data has the potential to introduce bias into the analysis results for the proposed statistical methods, or substantially reduce the precision of estimates related to treatment effects. If necessary, these issues will be dealt with using multiple imputation or Bayesian methods for missing data as appropriate.

## 15 PHARMACOVIGILANCE

### 15.1 Definition of Adverse Events

The European Clinical Trials Directive 2001/20/EC and applicable clinical trial regulations set out the legal requirements for adverse event recording, management and reporting of clinical trials.

**Table 3: Terms and Definitions for Adverse Events**

| Term                              | Definition                                                                                                                                                                                                                                    |
|-----------------------------------|-----------------------------------------------------------------------------------------------------------------------------------------------------------------------------------------------------------------------------------------------|
| Adverse Event (AE)                | Any untoward medical occurrence in a participant to whom a medicinal product has been administered, including occurrences which are not necessarily caused by or related to that product.                                                     |
| Adverse Reaction (AR)             | Any untoward and unintended response in a participant to an investigational medicinal product, which is related to any dose administered to that participant.                                                                                 |
| Unexpected Adverse Reaction (UAR) | An adverse reaction the nature and severity of which is not consistent with the information about the medicinal product in question set out in the Summary of Product Characteristics (SPC) or Investigator's Brochure (IB) for that product. |

|                                                                                                                        |                                                                                                                                                                                                                                                                                                                                                                                                                                                                                                                                           |
|------------------------------------------------------------------------------------------------------------------------|-------------------------------------------------------------------------------------------------------------------------------------------------------------------------------------------------------------------------------------------------------------------------------------------------------------------------------------------------------------------------------------------------------------------------------------------------------------------------------------------------------------------------------------------|
| Serious Adverse Event (SAE)
Serious Adverse Reaction (SAR)
Suspected Unexpected Serious Adverse Reaction (SUSAR) | 
Respectively, any adverse event, adverse reaction or unexpected adverse reaction that:
 

• results in death

• is life-threatening

• requires hospitalisation or prolongation of existing hospitalisation*

• results in persistent or significant disability or incapacity

• consists of a congenital anomaly or birth defect

 
Any other 'Important medical event(s)' that carries a real, not hypothetical, risk of one of the outcomes above.
 |
|------------------------------------------------------------------------------------------------------------------------|-------------------------------------------------------------------------------------------------------------------------------------------------------------------------------------------------------------------------------------------------------------------------------------------------------------------------------------------------------------------------------------------------------------------------------------------------------------------------------------------------------------------------------------------|

\*Hospitalisation is defined as an inpatient admission regardless of length of stay, even if the hospitalisation is a precautionary measure for continued observation. Hospitalisations for a pre-existing condition, including elective procedures that have not worsened, do not constitute a SAE.

## 15.2 Assessment of Adverse Events

The PI or designee is responsible for recording AEs observed. The PI or designee must assess all AEs for seriousness, causality, severity and if the adverse event is related to the study drug for expectedness.

## 15.3 Assessment of Causality

The PI or designee should make an assessment of causality, i.e. the extent to which it is believed that the event may be related to the study drug.

| Category    | Definition                                                                                                                                                                                  |
|-------------|---------------------------------------------------------------------------------------------------------------------------------------------------------------------------------------------|
| Definitely* | Temporal relationship of the onset, relative to administration of the product, is reasonable and there is no other cause to explain the event, or a re-challenge (if feasible) is positive. |
| Probably*   | Temporal relationship of the onset of the event, relative to the administration of the product, is reasonable and the event is more likely explained by the product than any other cause.   |
| Possibly*   | Temporal relationship of the onset of the event, relative to administration of the product, is reasonable but the event could have been due to another, equally likely cause.               |
| Unlikely    | Temporal relationship of the onset of the event, relative to administration of the product, is likely to have another cause which can by itself explain the occurrence of the event.        |
| Not Related | Temporal relationship of the onset of the event, relative to administration of the product, is not reasonable or another cause can by itself explain the occurrence of the event.           |

\* Where an event is assessed as possibly, probably or definitely related, the event is an AR.

